### Randomization

The study has a prospective, randomized, controlled, parallel-group design. Consecutive patients are randomly assigned to one of the two treatment study groups, labeled "Early PN" or "Late PN", using sequentially numbered, sealed and opaque envelopes. Upon addition of the study site Jessa Hospitals, these envelopes were replaced by an identical digital system allowing central computerized randomization. Patients are stratified per study site according to 17 primary diagnostic categories on admission. The stratified groups were labeled as follows:

I Medical-ICU admissions: (a) respiratory; (b) cardiovascular; (c) renal; (d) hematological/oncological; (e) GI/hepatic; (f) metabolic; (g) neurological (h) other;

II Surgical-ICU admissions according to referral discipline (a) cardiac surgery (elective or urgent surgery) (b) complicated thoracic surgery; (c) complicated vascular surgery (d) complicated abdominal and pelvic surgery (e) complicated neurosurgery (f) trauma and burns (g) transplantation (h) neurological disease (i) other.

Randomization - in a one to one allocation ratio - was performed using permuted blocks of 10, information that remained unknown to bed-side physicians and nurses, responsible for patient recruitment and therapy assignment.

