**Figure 3 F3:**
[figure not shown]
**CONSORT flow diagram**.

To assess compliance with the study protocol, the amounts of PN and EN actually given in the two study groups during the intervention window of 8 days will be reported as absolute numbers and percentages of target calories.

Discrete variables will be summarized by frequencies and percentages. Continuous variables will be summarized by use of either mean or standard deviations (SD) or median and interquartile range as appropriate.

Baseline and outcome variables will be compared using Student's t-test, (exact) Chi-square test and Mann-Whitney-U test, as appropriate.

All outcomes will be analyzed in an uncorrected manner as well as jointly corrected for risk factors (type and severity of illness, age, BMI and NRS categories). Type of illness will comprise the diagnostic categories, as stratified and grouped per organ system, as well as the presence or absence of a history of cancer. As severity of illness score for this correction, APACHE II will be used. BMI will be categorized as <20, 20-<25, 25-<30, 30-<40 and ≥40 kg/m2. Applicable NRS categories for this study are 3, 4, 5, 6 and 7. In case certain categories would appear underrepresented, such patients will be assigned to the next category in rank or previous category if it is the last category that is underrepresented.

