### Primary efficacy endpoint

The primary efficacy endpoint for this RCT is the time to discharge alive from ICU. As the time of ICU discharge to the regular ward may be affected by the availability of beds on the regular wards, which could induce bias, we a priori decided to analyze "time to discharge from ICU" as "time to ready for discharge from ICU". A patient is considered "ready for discharge" as soon as all clinical conditions for ICU discharge have been fulfilled (no longer in need for vital organ support and receiving at least 2/3 of the caloric requirements as oral feeds) or earlier when the patient is actually sent to a regular ward.

Time to discharge alive from ICU will be reported by Kaplan Meier plots, with ICU non-survivors censored beyond the longest ICU stay of survivors and censoring time of patients still in the ICU at closing of the datafile (90 days after last patient inclusion) over both treatment groups. The impact of "late PN" versus "early PN" will be analyzed, with and without correction for age, BMI & NRS categories and type and severity of illness, by Cox proportional hazard analysis. The distribution of the actual time to discharge from ICU will be reported for ICU-survivors and ICU-non-survivors separately. In view of the time window of the randomized intervention in ICU, also the proportion of patients staying beyond 8 days in ICU will be reported.

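### Randomization uses site and 17 diagnostic categories, but the models omit site and group the categories, and neither the corrected nor the uncorrected result is named as deciding

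*Protocol article*

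**What the plan says.** The Randomization section sets the strata: "Patients are stratified per study site according to 17 primary diagnostic categories on admission". Allocation was "in a one to one allocation ratio" and "was performed using permuted blocks of 10".

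Under General rules of the statistical analyses, each outcome is analysed twice: "All outcomes will be analyzed in an uncorrected manner as well as jointly corrected for risk factors". The correction set is type of illness, APACHE II as the severity score, age, BMI category and NRS category. Diagnosis enters as follows: "Type of illness will comprise the diagnostic categories, as stratified and grouped per organ system", together with a history of cancer. The simple comparisons are unstratified: "Baseline and outcome variables will be compared using Student's t-test, (exact) Chi-square test and Mann-Whitney-U test, as appropriate".

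The Primary efficacy endpoint section repeats the pairing for time to discharge alive from ICU: "with and without correction for age, BMI & NRS categories and type and severity of illness, by Cox proportional hazard analysis". The Safety endpoints and Secondary efficacy endpoints sections use the same covariate list. Site is in none of these lists, no stratified test is planned, and no section says which of the paired results carries the conclusion.

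**The concern.** Randomizing in blocks within strata balances the arms on those strata, so the true sampling variation of the treatment comparison no longer contains the between-stratum differences. An analysis that ignores the strata does not take credit for that balance. The loss matters only if the strata predict outcome, and the plan indicates that they do: the subgroup rationale says cardiac surgery patients spend less time in ICU, and type of illness is treated as a risk factor.

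Two things are at stake. One is power: the Rationale and the Discussion both say that a neutral result would support withholding parenteral nutrition for a week, so a conservative test works in favour of one of the stated conclusions. The other is the decision rule. The primary endpoint yields two Cox p-values, each judged at 0.05, with nothing fixed for the case where they disagree. The two hazard ratios are also not the same quantity, because a Cox hazard ratio changes when prognostic factors are added even if the arms are balanced on them.

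**Working it through.** **Inputs from the protocol.** 2320 patients per arm; ICU stay 8 ± 13 days with a 1-day difference, one-tailed on the raw scale; ICU mortality 20% with a 3-point change, two-tailed, 70% power (Sample size calculation). Blocks of 10 and 17 categories per site (Randomization). Two sites, hence 2 × 17 = 34 strata, is inferred from the text.

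**Assumption.** The share of outcome variance explained by the strata, R², is not given. The range 0.01 to 0.30 is used.

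**1. The plan's own figure.** For 20% versus 23%, two-sided 5%, 70% power:
n per arm = [1.960·√(2·0.215·0.785) + 0.524·√(0.20·0.80 + 0.23·0.77)]² / 0.03² ≈ 2315, or 4630 in total. The stated 4640 reproduces. At 2320 per arm, power for the 1-day difference is Φ(1/0.3817 − 1.645) = 83.5% one-tailed, where 0.3817 = 13·√(2/2320).

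**2. Linear comparison, strata ignored versus strata used.** Interval too wide by the factor 1/√(1−R²); true two-sided alpha = 2·[1 − Φ(1.96/√(1−R²))]; one-tailed power with strata = Φ(2.620/√(1−R²) − 1.645).

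| R² (assumed) | Interval too wide by | True alpha, strata ignored | One-tailed power, strata used (83.5% planned) |
|---|---|---|---|
| 0.01 | 0.5% | 0.049 | 83.8% |
| 0.05 | 2.6% | 0.044 | 85.2% |
| 0.10 | 5.4% | 0.039 | 86.8% |
| 0.20 | 11.8% | 0.028 | 90.0% |
| 0.30 | 19.5% | 0.019 | 93.1% |

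**3. What the corrected model still loses.** Simulated linear model on log stay: 4640 patients, 34 strata, blocks of 10, 1000 trials per setting. The 25/75 medical/surgical split is the protocol's; the category shares, 10% of patients at the second site and a nine-group organ-system collapse are assumed. APACHE II, age, BMI and NRS were not modelled. Mean standard error relative to full strata:

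| Total strata R² | Uncorrected | Grouped, no site | 17 categories, no site |
|---|---|---|---|
| 0.06 | 0.03338/0.03236 = 1.03 | 0.03296/0.03236 = 1.02 | 0.03253/0.03236 = 1.005 |
| 0.11 | 0.03337/0.03149 = 1.06 | 0.03253/0.03149 = 1.03 | 0.03167/0.03149 = 1.006 |
| 0.22 | 0.03338/0.02949 = 1.13 | 0.03161/0.02949 = 1.07 | 0.02986/0.02949 = 1.013 |

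**4. The Cox setting.** Log-rank/Cox score test in the same design, with deaths (assumed 10%) censored beyond the longest stay and an assumed treatment log hazard ratio of 0.08:

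| Strata log-hazard SD | SD of unstratified z under the null | Power unstratified | Power stratified |
|---|---|---|---|
| 0.3 | 0.978 | 27% | 30% |
| 0.5 | 0.989 | 26% | 35% |
| 0.8 | 0.976 | 17% | 31% |

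Those null SDs imply a true alpha of 2·[1 − Φ(1.96/SD)], about 4.5% to 4.8%. The power values are low because the effect chosen is small; only the contrast is informative. A separate Cox simulation at a strata log-hazard SD of 0.5 gave the same standard error with and without strata (0.031), a log hazard ratio of 0.027 without and 0.032 with them, and power of 12% versus 16%. In a simulated logistic model the standard error was slightly smaller without the strata (0.0705 versus 0.0734). In both models, then, the loss comes through attenuation of the estimate.

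**The case against.** The strongest defence is that the plan already adjusts for most of what matters. Every outcome has a corrected analysis with diagnosis, cancer history, APACHE II, age, BMI and NRS, so a comparison of no adjustment with full strata overstates the gap. This stands, and it is why the remaining loss is small.

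Four stronger readings are tempting, and the document does not support them.

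- A reader might infer that the main Cox and mortality intervals are 5% to 12% too wide, or that their alpha is 3.9% or 2.8%. Those are linear-model values and do not carry over to Cox or logistic models.
- A reader might calculate that power rises from 74.5% to 79% or 83%. That starts from a two-tailed raw-scale t-test. The plan powers the trial with a one-tailed raw-scale test, confirmed by a two-tailed test on the log scale, and analyses the endpoint by Cox regression.
- A reader might infer that site is known to drive discharge. The text does not say so. The endpoint is readiness for discharge on clinical criteria, and ventilator weaning follows one guideline in all units. Earlier actual transfer to a ward still counts, so site differences remain plausible but unproven.
- A reader might infer that grouping merges medical with surgical patients of one organ system. The wording allows this, but the final groups are not stated.

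It could also be said that such detail belongs in a separate analysis plan. However, the article presents itself as that plan for the primary report and states the covariate list in several sections. The absence of site and of a deciding analysis is therefore a feature of what it fixes, not of condensation.

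**Conclusion.** The point holds as a matter of efficiency and decision rule. The uncorrected analyses err on the conservative side, and nothing here inflates type I error or threatens validity. The size depends on how strongly the strata predict outcome, which the protocol does not give; at R² = 0.01 the loss is negligible. The small remaining loss in the corrected models was estimated for a linear model with an assumed patient mix and grouping, and was not simulated for the corrected Cox model. The missing decision rule depends on none of these assumptions. It is worth settling, because the uncorrected Cox estimate is expected to lie nearer 1 than the corrected one.

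**What to change.** Name one primary analysis: a Cox model stratified by, or adjusted for, study site and the randomization categories, with sparse cells pooled within medical or within surgical admissions, and with age, APACHE II, BMI and NRS as covariates. Adding site and ungrouped categories as covariates to the planned model would do nearly the same as stratifying. Use the same factors in the mortality models, and label the uncorrected analyses as supportive. If any grouping of categories is kept, list the groups.

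The cost is a change of plan wording and a pooling rule for sparse strata, which should be fixed without reference to outcome by arm. Site and category are recorded for every patient at randomization, so no new data are needed.

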#### a. Randomized interventions

##### "Early PN"

Patients randomized to the "early PN" group receive Glucose 20% at 40 ml/hr on the admission day. PN [OliClinomel^® ^or - when fat free PN is indicated - Clinimix^® ^(Baxter, Brussels Belgium)] is initiated the second morning in ICU. The amount of PN to be given on any particular day is the difference between calculated caloric needs and the calories delivered by EN the previous 24 hours. Caloric needs calculations are based on corrected ideal body weight, age and gender [32] moreover, we defined an absolute maximal target of 2880 kcal/day. When EN covers 80% of calculated caloric needs, PN is stopped. When the patient is able to eat, the PN is reduced and eventually stopped. Whenever enteral or oral intake falls below 50% of calculated caloric needs, the PN is restarted.

##### "Late PN"

Patients randomized to the "late PN" group receive a volume of Glucose 5% that is required to obtain adequate hydration taking into account the volume of EN that is being delivered. If enteral feeding of at least 80% of the calculated calories is not possible after 7 days in ICU, PN is initiated on day 8.

#### b. Common strategy for early EN in both study arms

In all patients unable to eat on the second evening of ICU stay and without formal contraindication, EN is initiated with the patients in semi-recumbent position. The increase of EN volume, the use of gastroprokinetics and duodenal feeding tubes are described in the standing-orders for EN. Parenteral trace elements, minerals and vitamins are administered in all patients of both groups as clinically indicated.

In both study groups, blood glucose levels are targeted to 80-110 mg/dl with continuous insulin infusion [18]. Blood glucose and potassium are monitored every 1 - 4 hours on the bloodgas-analyzer (ABL-Radiometer^®^) using arterial blood samples.

The volumes of PN and EN to be given according to the treatment group are calculated by the PDMS (Metavision^®^, iMDsoft, Boston, USA). These calculations are based on the nutritional intake during the previous day and the clinical evolution of the patient. Patients are weaned from the ventilator according to a standardized guideline used in all participating ICUs. End-of-care decisions in patients for whom further intensive care is considered to be futile are taken in consensus by a group of two senior ICU physicians and the referring specialist.

#### Handling of re-admissions to ICU

Patients who are re-admitted to ICU after a participation in EPaNIC are not eligible for re-inclusion. Patients who are readmitted to the ICU within 48 hours of discharge and who are still within the 7 days time window of the initial randomization receive the nutrition-schedule they were assigned to during the initial ICU admission. Patients readmitted later will be fed at the discretion of the attending physician.

#### Blinding of treatment allocation

Treating physicians and patients could obviously not be blinded. However, all outcome assessors, which are investigators not directly involved in the patients care (such as statisticians, laboratory personnel, infectious disease specialists, pathologists, physiotherapists involved in the strength measurement, electrophysiologists) as well as physicians and nurses in the conventional wards, are blinded to treatment allocation.

#### Data collection following recruitment

All medications received by the patients during ICU stay are registered. Every day the amount of kilocalories, lipids, proteins, carbohydrates delivered by either PN or EN are calculated from the PDMS in an automated manner and entered into the case report form (CRF). For calculation of the energy requirements, 50% of the gastric residual volume, which is being discarded by the bedside nurses, is considered to be EN calories not absorbed by the patient. Interruptions of EN delivery and predefined digestive intolerance are registered daily. Mechanical complications such as displacement or obstruction of the enteral feeding tube or the central venous catheters; and clinical complications such as pneumothorax, hemothorax and subclavian or carotid artery puncture are recorded daily. Number of ICU days with a central line in situ is also noted. In addition we record the need for and the number of days of mechanical ventilatory support, of mechanical and pharmacological hemodynamic support, of renal replacement therapies and placement of tracheostomy.

Blood samples (a subset of which are immediately stored on ice for future endocrinological measurements) are taken upon ICU admission and daily at 06:00 h until discharge from ICU or death. All whole blood glucose levels are measured on arterial blood using a blood gas analyzer on each ICU and are registered for later calculation of glucose metrics.

Analyses on blood and urine for the primary clinical analyses include routine chemistry, hematology, and markers of inflammation. Further metabolic, endocrine and inflammatory measurements planned on stored samples in the context of mechanistic analyses fall beyond the scope of this paper. In addition, for later mechanistic studies, a random selection of patients are prospectively and repeatedly screened for the presence of sludge or cholecystitis on ultrasonography.

All new infections of the lungs, the blood stream, the urinary tract and wounds are recorded by an infectious disease specialist. Bacteraemia is further classified by responsible pathogen and as catheter related blood stream infection versus other bacteraemia [33,34].

For further mechanistical and exploratory studies, elaborated muscle strength testing, electrophysiological examination, skeletal muscle and adipose tissue biopsies and radiological evaluation of skeletal muscle and adipose tissue compartments are performed after specific or additional informed consent from the patient or the legal guardian. These analyses will be repeated at different time intervals, also after hospital discharge, on condition of obtaining adequate additional funding. The statistical plan for all these analyses fall beyond the scope of this manuscript. Furthermore, as far as practically feasible, every patient is approached just prior to hospital discharge, for a 6 minute walking distance test (6 MWD) [35] by a trained physiotherapist and for scoring the activity in daily life (ADL). The long-term follow-up will include sending out a Medical Outcomes Study 36 items short form questionnaire to all patients.

#### Data conservation and processing

Data are collected electronically in an anonymized CRF, unambiguously linked to the source file. Data is manually transferred (and checked for accuracy) into the CRF by the clinical research assistance team on a daily basis from the ICU PDMS and the Leuven University Hospitals Clinical Working Station (KWS). Extensive range and consistency checks are performed by the study monitor. Vital status at 90 days will be recorded for all patients, eventually via the Belgian National Registry when this information is not available in the hospital information system.

## Trial Organisation

### Administrative and legal aspects

The sponsor (K.U.Leuven) provides direct access to the CRF, the source data and the study master file for monitoring, Independent Ethics committee review and regulatory inspection. The sponsor established an independent data safety monitoring board (DSMB) (RB, PL and JV). The sponsor appointed one monitor (PW). The monitor verifies that the trial is performed in accordance to the protocol as described in the European Medicine Agency's "Note for guidance on good clinical practice CPMP/ICH/135/95." as well as the Declaration of Helsinki. Monitoring is performed and reported following the sponsor's standing operating procedures. No fault insurance is covered by Fortis Corporate Insurance NV.

### Trial Coordination

The clinical research team guarantees a daily follow up of patient screening and inclusion, availability of requested clinical data in the clinical patient files and protocol compliance. Every non-compliance to the protocol and other questions or problems are reported to the study monitor (PW) and discussed with the principal investigators. Serious Adverse Events (SAE) are reported to the study sponsor (K.U.Leuven). The study monitor (PW) regularly provides the sponsor with reports on inclusions and SAE. Regular meetings are organized with principal investigators and clinical research team to discuss the daily progression of the research project.

### Protocol implementation

The protocol was and is being instructed (by MC) to all clinical medical and paramedical staff trough frequent teaching sessions, clinical feedback rounds and posters representing the study flow. (Figure 2) The protocol decision support is integrated into the ICU patient data management system, facilitating the prescription of the exact amounts of PN and EN according to protocol and clinical evolution. ([name], DC, GM and MC)

**Figure 2 F2:**
[figure not shown]
**Trial procedures flow sheet**.

### Interim analysis

As both the nutritional strategies investigated in this trial are current ICU practices, the DSMB judged that repeated interim analyses for efficacy were not required. One formal "safety" interim analysis was planned after patient number 1500 left the ICU, during which the independent DSMB had access to un-blinded results on ICU mortality, hospital mortality and serious adverse events from 1495 patients. The DSMB judged that there was no reason to prematurely stop the clinical trial for safety reasons, or to perform more safety interim analyses and decided that the randomization and nutritional therapy study had been executed as planned in the study protocol. The DSMB advised to continue the study to completion, under monitoring of the serious adverse events. Because the primary efficacy endpoint was not analyzed, no correction of the significance level at the final analysis is necessary.

## Statistical analysis plan

We here report the statistical analysis plan for the primary clinical report of the primary and secondary clinical endpoints of this RCT. These include the acute clinical effects of the intervention during ICU stay and hospitalization, including survival up to 90 days after randomization. Additional long-term outcomes, further mechanistic and exploratory analyses of the effect of early PN versus late PN will be reported separately and statistical details for these additional studies fall beyond the scope of this manuscript. The additional outcomes comprise, among others, results of elaborated peripheral and respiratory muscle testing and electrophysiological signs of myopathy-neuropathy, radiographic and microscopic evaluation of muscle and adipose tissue volumes and composition, biochemical and molecular analyses of skeletal muscle and adipose tissue biopsies, endocrine function, liver and bile function. Furthermore, a health economy analysis is planned.

### General rules of the statistical analyses

A consort diagram will be reported. (Figure 3) All analyses will be performed on a full intention-to-treat basis. The data file will be finalized 90 days after inclusion of the last patient.

